### Control territories

Each control territory is chosen to be as similar as possible to each corresponding TSN project territory, based on simple quantitative indicators. The identification method has already been used in France for the evaluation of another public policy (implementation of a minimal income for low-income people). Each control territory is chosen in the same region as the TSN project territory to control for regional policy effects. It must have roughly the same size as the TSN project territory, be a compact geographical zone and not be too geographically close to the TSN project territory, in order to avoid contamination. The selection process, described elsewhere, is carried in three steps:Constitution of a list of candidate control territories, according to geographic, demographic and healthcare offer criteria;Sorting of the list according to the territory’s structural similarity with the TSN project territory, based on a set of 20 criteria classified in four categories: 1) population demographic characteristics influencing healthcare demand; 2) population social and economic characteristics; 3) population health and 4) healthcare offer. The similarity analysis is based on factorial analyses;Determining the territory that is the most similar to the TSN amongst the subset of candidate territories, according to the number of emergency room visits’ evolution, which is potentially influenced by TSN projects effects. This analysis is based on time series models. Were also considered in the final choice: feasibility of data collection and existence of competitive interventions in the territory.

### Data analysis and interpretation

Analysis involves quantitative, qualitative and data visualisation approaches.

Quantitative analyses in axes 2, 3 and 4 mostly rely on a set of standardized indicators which represent the outcomes supposedly influenced by the TSN projects in quality and intensity of healthcare consumption or medical practices. These indicators are calculated on an annual or quarterly basis and compared over time (between T0, T1 and T2). Adjustment is done through direct standardization depending on the scope of the indicator: by age and sex for general population-based measures and, to the extent possible, by clinical and social background for indicators focused on particular populations (the elderly, patients witch chronic diseases…).

Statistical estimations are then performed to assess the impact of TSN projects outcomes, with inherent limitations. First, no overall influence of TSN projects can be produced, given the variety of services provided and the disparity from one region to another: estimations are thus restricted to particular services. Second, for both technical and methodological reasons, estimation cannot be performed on subsamples of TSN users, neither for patients nor for health professionals. Instead, estimates are calculated on the whole populations targeted by the services when relevant: elderly people with functional impairments for the coordination service, young adults for vaccination reminders, patients with chronic diseases (diabetes, heart failure…) for serious games or connected devices, etc.

This approach is usually referred to as “intention-to-treat” estimate (ITT), by contrast to local average estimates (LAE) calculated on program takers/users only. Causal effects of TSN services can then be assessed if and only if i) services are exclusively intended to specific subgroups of patients, ii) these groups can be routinely identified in SNIIRAM data and iii) there is a sufficient share of actual users of the services within these groups (otherwise, variance of ITT estimate is getting too large). For axis 1 analysis, indicators of TSN use, implementation and of TSN users characteristics will be described.

Qualitative analysis of axes 1, 2 and 3 is based on interviews which are recorded, anonymous, integrally transcribed and imported into the NVivo11 software to achieve a thematic content analysis. This method aims "at spotting, in verbal or textual expressions, recurring general themes that appear under various more concrete content" [35]. This type of analysis intends to "proceed systematically in the identification, consolidation and, alternatively, the discursive examination of themes in a body"[36]. The construction process of these thematic categories, coding, is both inductive and deductive because the development of themes and sub themes rests on both literature and emerging categories of empirical analysis. The exploratory qualitative studies require in-depth exploration of these emerging categories (Grounded Theory method).

Qualitative investigations point out political and organizational barriers to implementation (axis 1), the conditions of acceptance of HI Technology and organizational innovations, the TSN program’s effects on healthcare work and professional coordination practices (axis 3), the changes in care pathway if they are significant for the patient and their family caregivers (especially patient empowerment) (axis 2).

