### The interventions – the TSN projects

All the TSN projects develop digital services for healthcare users and healthcare and social care producers (hospitals, ambulatory sector, medico-social sector) to improve healthcare coordination, collaboration between professionals and access to healthcare and prevention information and professional guidelines (Table 1).

**Table 1 Tab1:** Presentation of digital/E-services and functionalities in each TSN project area – EvaTSN project, France

Type of E Health Services	E Health-services functionalities	AQT	BGN	IF	LR	RHA
Organisation of healthcare coordination^a^	- Platform for service coordination	✓	✓	✓	✓	✓
	- Digital coordination service	✓	✓	✓	✓	✓
	- Call center for informal caregivers					✓
E-services for users/patients	- Diffusion service of general healthcare information	✓	✓	✓	✓	✓
	- Medical information management services	✓	✓	✓	✓	✓
	- Administrative information management services	✓	✓	✓	✓	✓
	- Community of connected patients				✓	
E-services for professionals	- General health information service	✓	✓	✓	✓	✓
	- Professionals' patient medical information management	✓	✓	✓	✓	✓
	- Administrative information management services	✓	✓	✓	✓	✓
	- Community of connected professionals		✓	✓		✓
Administrative and monitoring services for policy makers	- Administrative monitoring	✓	✓	✓	✓	✓
	- Epidemiological monitoring		✓		✓	✓
	- eHealth innovation promotion	✓	✓	✓	✓	✓
	- Interoperability management	✓	✓	✓	✓	✓

^a^between healthcare producers and between health care producers and patients, *AQT* aquitaine, *BGN* Bourgogne, *IF* Ile-deFrance, *LR* La Réunion, *RHA* Rhône-Alpes

Most TSN projects target patients with chronic conditions or elderly dependent people. Some of them focus on patients suffering from specific diseases, including congestive heart failure (Aquitaine, Bourgogne, la Réunion regions), cancer (Bourgogne, Ile-de-France regions), stroke (Bourgogne), respiratory failure (Aquitaine), or specific populations, including young people (Bourgogne), pregnant women (Ile-de-France), obese and disabled people (la Réunion), and situations of social vulnerability (Bourgogne, Ile de France).

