Impact evaluation using different dimensions is also needed. We evaluate the effect of TSN projects on final and intermediate health outcomes (for example: prevalence of drug overuse or misuse, prevalence of hospital admissions’ appropriateness, incidence of chronic diseases, etc.) and on patient satisfaction and experience with HI supports and coordination [42].

TSN projects are developed in five territories with rather similar size (about 200 000 inhabitants) and social profiles (high proportion of low-income population). They are geographically spread in five regions on the whole French territory and have both rural and urban areas. They represent the geographical diversity of the French territory. This may favour a good external validity of the study.

This complex evaluation has many methodological challenges.

We have to develop a common evaluation framework for five TSN projects with several HI technology components targeting different populations. This implies to have a good knowledge of all the TSN projects components, to identify the common core components of TSN projects, to have a good understanding of their action mechanisms and to rely on many dimensions (structure, process, and outcome) covering the whole spectrum of potential TSN projects’ effects. This diversity may improve mainly the external validity of our conclusions thus allowing the identification of the most effective HI technology interventions.

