Another methodological challenge is linked to the gap between the evaluation and the TSN project intervention level. Each TSN project is focused on specific conditions or diseases (specific chronic conditions, social vulnerability situations, elderly dependant people, etc.) and includes samples of patients and people presenting these conditions (“TSN patient users”). Our main quantitative analyses use data from the French National Heath Insurance Database (SNIIRAM database). As it is impossible to identify the TSN patient users individually speaking, we need to select groups of people presenting similar characteristics as those targeted in the TSN projects and living in the TSN territory (“TSN targeted people”) using validated algorithms. This lack of specificity in TSN projects evaluation may lower the strength of the association between TSN projects interventions and outcomes. However the estimates correspond to the real impact assessment of TSN project at a moderate development stage. Only qualitative analyses can precisely and specifically identify and interview TSN projects users (“TSN patient users” or “TSN professional users”), in complementary means of quantitative analyses.

The third methodological challenge is linked to the controlled before-after study design. We make the strong hypothesis of the comparability of each TSN project territory with its control at the beginning and throughout all the TSN projects implementation and evaluation. We use a precise and proven method to identify the control TSN project territories, based on structural and social similarity. However, a strong hypothesis is that the control and the TSN project territories are subject to the same external factors that may influence evaluation criteria.

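### The three criteria for a causal service effect do not exclude co-delivered TSN services, so a targeted-group contrast may be a bundle effect rather than the effect of one service

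*Protocol article*

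**What the plan says.** In Methods, Data analysis and interpretation, the article rules out one overall TSN effect because the services differ between regions, and concludes that "estimations are thus restricted to particular services". It also rules out analysis of users alone; instead, "estimates are calculated on the whole populations targeted by the services when relevant". Its examples are elderly people with functional impairments (coordination service), young adults (vaccination reminders) and patients with chronic diseases (serious games or connected devices).

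It then gives the conditions for assessing causal effects of services, worded as both necessary and sufficient:

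- (i) "services are exclusively intended to specific subgroups of patients"
- (ii) "these groups can be routinely identified in SNIIRAM data"
- (iii) "there is a sufficient share of actual users of the services within these groups"

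Table 1 (The interventions – the TSN projects) lists the functionalities by territory. "Digital coordination service", for example, is ticked in all five.

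The Discussion explains the choice of population: "As it is impossible to identify the TSN patient users individually speaking", groups sharing the targeted characteristics are selected by algorithm. It says that this lack of specificity may weaken the observed association. Elsewhere it says that the diversity of projects may help external validity, "thus allowing the identification of the most effective HI technology interventions".

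**The concern.** A service meant only for subgroup S is not the same as a subgroup S that is offered only that service. Attribution to a single service needs the second statement, or a contrast that takes the other services out. The article states only the first and presents the list as sufficient.

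At stake is what the results can be said to show. The Discussion expects them to support health care management and policy decisions. A change credited to one service could come wholly or partly from another service deployed in the same territory. The disclosed limitation covers dilution only. Co-delivered services can push an estimate either way, and that is not mentioned.

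**Working it through.** The article gives no figure for the size or precision of the impact estimates, so there is none to reproduce. The check concerns identification.

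**1. What each criterion controls.**

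| Criterion | Controls | Limits other TSN services in the subgroup? |
|---|---|---|
| (i) exclusive targeting | who the service is for | No |
| (ii) identifiable in SNIIRAM | whether the subgroup can be extracted | No |
| (iii) sufficient share of users | precision (the text's own reason is variance) | No |

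**2. Co-availability, counted from Table 1.**

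| Block | Rows | Ticked in all five territories |
|---|---|---|
| Healthcare coordination | 3 | 2 |
| Users/patients | 4 | 3 |
| Professionals | 4 | 3 |
| Policy makers | 4 | 3 |
| Total | 15 | 11 |

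The policy-maker rows are not services that patients receive. Without them, 2 + 3 + 3 = 8 of 3 + 4 + 4 = 11 functionalities are in every territory. The same section says that most projects target chronic or elderly dependent patients, so the populations in the examples live where these services are offered.

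**3. What the contrast estimates.** If effects add up and the control area follows the same trend, the before-after contrast in subgroup S is approximately

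D(S) = Σ over services k of [uptake of k in S × effect of k per user in S].

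Only D(S) is observed. Users are not identified, so the terms cannot be separated within a territory.

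**4. Illustration.** Uptakes and effects here are assumed; the article gives none. Effects are in percentage points per user.

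| Studied service | Other services | D(S) |
|---|---|---|
| uptake 10%, effect −2 | no effect | 0.10 × (−2) = −0.2 |
| no effect | uptake 10%, effect −2 | 0.10 × (−2) = −0.2 |
| no effect | uptake 30%, effect −2 | 0.30 × (−2) = −0.6 |
| uptake 10%, effect −2 | uptake 30%, effect −2 | −0.2 − 0.6 = −0.8 |
| uptake 10%, effect −2 | uptake 10%, effect +2 | −0.2 + 0.2 = 0 |

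The first two rows give the same observed value from opposite truths. The last hides a real effect.

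**5. Can differences between territories separate the services?** Code Table 1 as 0/1 for five TSN territories and add five control rows of zeros. The 15 columns have rank 5. The 11 universal columns are identical and equal the TSN-versus-control indicator, so only their sum is estimable. The other four functionalities (in 1, 1, 3 and 3 territories) separate only on paper: 5 parameters on 5 territory contrasts leaves 5 − 5 = 0 residual degrees of freedom, with strict additivity and no territory effect assumed. On the 11 non-policy rows the rank is 4.

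**6. The article's own examples.**

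- *Connected devices or serious games in chronic disease:* coordination and information services could affect the same outcomes, and two kinds of service are named for one population. The problem is strongest here.
- *Coordination service in elderly people:* coordination is itself the service under study, so the problem is weaker.
- *Vaccination reminders in young adults:* if the outcome is vaccination, few other services would move it. The problem is small.

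**The case against.** The strongest reply is that co-exposure is not documented. Table 1 shows what each project includes, not uptake, timing or reach by subgroup, and the Discussion says that parts of some projects are still in development. This stands: the article shows that other services are on offer, not that the subgroup uses them at the same time. It bounds the claim but does not make the three criteria sufficient, since none asks the question.

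The matrix check is also limited. Connected devices, serious games and vaccination reminders are not rows of Table 1, and targeted diseases differ between territories (heart failure in three regions, stroke in one). The check shows that Table 1 alone cannot separate the services. It is not a proof for every possible analysis.

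Three stronger readings are tempting but unsupported:

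- *All service estimates are confounded to a similar degree.* The examples above differ widely.
- *Each estimate is overstated by the full effect of the shared services.* Neither size nor direction follows from the article. If rate reductions of, say, 10% (shared) and 20% (studied) act proportionally, the total is 1 − 0.90 × 0.80 = 28%, an excess of 8 points and not 10. The Background also cites unintended effects of such technologies, so a shared service could pull the other way.
- *The study promises to rank services.* The Discussion sentence is hedged, is not among the stated objectives, and may draw on the qualitative and process evaluation. No ranking analysis is described.

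Finally, differing external shocks between territories are already covered by the article's comparability hypothesis and are not part of this point.

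**Conclusion.** The point holds as a defect in what the article states, not as a detail left to an analysis plan: it sets out the causal conditions itself, as sufficient, and they are not. Criteria (i) to (iii) can all be met while the estimate reflects other services of the same territory. The documented extent is availability: 8 of 11 coordination, patient and professional functionalities in all five territories. The resulting error in any estimate is unknown in size and sign, and depends on uptake of the other services in the subgroup and on whether they act on the outcome concerned. The conclusion assumes only that some service offered to a subgroup beside the studied one could affect the same outcome. Where that is implausible, the criteria suffice on this point. The change should be made, because it alters what the study may conclude.

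**What to change.** 1. In Data analysis and interpretation, add a fourth condition: no other TSN service offered to the subgroup plausibly affects the same outcome, or a stated contrast removes its effect. Record the judgement for each service-outcome pair.
2. Where the condition is not met, report the estimate as the effect of the territory's TSN bundle in that population, not of the single service.
3. In the Discussion, limit the sentence on the most effective interventions to hypothesis generation. State beside the dilution caveat that co-delivered services may bias a service-specific estimate in either direction.
4. Optionally, as a sensitivity analysis, use SNIIRAM for a triple difference: targeted minus non-targeted residents, TSN minus control territory, after minus before. State its assumption that shared services act equally in both groups, which is doubtful for services aimed mainly at chronic or elderly patients. Note too that it does not separate services aimed at the same group. It should not be the sole definition of a service effect.

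Items 1 to 3 cost only wording and a short table; the price is fewer estimates called service effects and more modest conclusions. Item 4 needs indicators for non-targeted residents and one more interaction term. With an equal-size, independent comparison group of equal variance the standard error rises by √2, about 1.4 times; it rises less with a larger group, and need not rise if territory shocks common to both groups cancel.

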### Monitoring and coordination

Audits of the conduct of the study are done every six months by the jury of the call, independently from the French Health Ministry. The EvaTSN project follow-up is also done yearly by an Independent Advisory Board.

### Ethical considerations

The complexity of the evaluation implies separate approval for different facets. This study has been approved by the French National Institute of Health Data (IDS – Institut des données de santé). Approval by the national CCTIRS (Comité consultatif sur le traitement de l'information en matière de recherche dans le domaine de la santé) and the CNIL (Commission nationale Informatique et Libertés) has been obtained for SNIIRAM and for qualitative analyses.

Participants in qualitative analyses (semi-directive interviews) are guaranteed strict confidentiality of records and of all statements through an encrypted identifier for each participant. Each participant fills in an informed consent form before the beginning of the study, given to the sociologist in charge of the qualitative analyses. The files and audiorecordings are kept in a sealed location of the research centre, with access limited to the qualitative analysis researchers of the EvaTSN research group, and will be destroyed after 15 years. No name will appear on any public documents and no information will be divulged that could allow participants to be identified by a third party. The EvaTSN research group members have access to anonymous quantitative datasets. All the quantitative analyses and quantitative data collection from questionnaire or databases are strictly anonymous.

Results will be disseminated as a report to the French Health Ministry. An disseminating plan to participants is in discussion with the French Health Ministry. Authorship of articles is defined according to the Vancouver Convention.

## Discussion

We expect the project to add information on HI technology effectiveness, efficiency, and effectiveness determinants in the French healthcare system. It should produce key elements for HI technology effective development and for structuring further evaluation of HI technology impact.

Many authors point out that there is a lack of evidence-based HI technology which is much needed [21, 24, 32]. Results from these studies could pave the way to a strong evidence-based implementation strategy of digital technologies in a local system, aiming at providing patient-centred and quality-assured coordinated care.

Moreover, many authors acknowledge the lack of care coordination in developed countries and the need to build and test interventions to improve care coordination [37]. Some trials testing the impact of HI technology intervention on care coordination are ongoing or already carried out in American and European countries, focusing on several conditions (depression, cardiovascular disease, cognitive impairment) [38–40]. But many HI technology interventions still need to be designed and tested in a variety of settings. Care coordination is the next opportunity and challenge for HI technology. Recently, a call to methodologically robust research on HI technology impact on care coordination was launched by the International Medical Informatics Association (IMIA) [24]. Our research project is the first one conducted in France which covers such a large perimeter of types of care and disorders or patient conditions.

Since complex interventions like HI technology include multiple components that are interrelated or interdependent, it can be challenging to develop, document, evaluate and report on them [41]. Our project will apply the principles of complex intervention evaluation, combining quantitative and qualitative analyses, conducting impact and process evaluation with multiple evaluation criteria collected from different sources (“TSN targeted people”, “TSN patient users”, “TSN professional users”, TSN developers and stakeholders, French National Heath Insurance Database). Process evaluation is essential for different reasons. It allows the understanding of the right contexts for HI technologies and their components to serve as an essential support to the delivery of patient-centred, coordinated, and quality-assured care. It also allows the evaluation of organizational changes that are paramount for the impact of new HI technology tools.

Impact evaluation using different dimensions is also needed. We evaluate the effect of TSN projects on final and intermediate health outcomes (for example: prevalence of drug overuse or misuse, prevalence of hospital admissions’ appropriateness, incidence of chronic diseases, etc.) and on patient satisfaction and experience with HI supports and coordination [42].

TSN projects are developed in five territories with rather similar size (about 200 000 inhabitants) and social profiles (high proportion of low-income population). They are geographically spread in five regions on the whole French territory and have both rural and urban areas. They represent the geographical diversity of the French territory. This may favour a good external validity of the study.

This complex evaluation has many methodological challenges.

We have to develop a common evaluation framework for five TSN projects with several HI technology components targeting different populations. This implies to have a good knowledge of all the TSN projects components, to identify the common core components of TSN projects, to have a good understanding of their action mechanisms and to rely on many dimensions (structure, process, and outcome) covering the whole spectrum of potential TSN projects’ effects. This diversity may improve mainly the external validity of our conclusions thus allowing the identification of the most effective HI technology interventions.

Another methodological challenge is linked to the gap between the evaluation and the TSN project intervention level. Each TSN project is focused on specific conditions or diseases (specific chronic conditions, social vulnerability situations, elderly dependant people, etc.) and includes samples of patients and people presenting these conditions (“TSN patient users”). Our main quantitative analyses use data from the French National Heath Insurance Database (SNIIRAM database). As it is impossible to identify the TSN patient users individually speaking, we need to select groups of people presenting similar characteristics as those targeted in the TSN projects and living in the TSN territory (“TSN targeted people”) using validated algorithms. This lack of specificity in TSN projects evaluation may lower the strength of the association between TSN projects interventions and outcomes. However the estimates correspond to the real impact assessment of TSN project at a moderate development stage. Only qualitative analyses can precisely and specifically identify and interview TSN projects users (“TSN patient users” or “TSN professional users”), in complementary means of quantitative analyses.

The third methodological challenge is linked to the controlled before-after study design. We make the strong hypothesis of the comparability of each TSN project territory with its control at the beginning and throughout all the TSN projects implementation and evaluation. We use a precise and proven method to identify the control TSN project territories, based on structural and social similarity. However, a strong hypothesis is that the control and the TSN project territories are subject to the same external factors that may influence evaluation criteria.

We face other difficulties. First, the French Health Ministry has given a short schedule. First conclusions should be given in 2017 and the evaluation should be finished in 2018. It is a very short time as the TSN projects are still being implemented and moreover, parts of some projects are in ongoing development. It is a real difficulty for the production of conclusions about TSN program health impact because we will not be able to see all the TSN projects' effects yet at that time. The HI technology evaluation model will be however described. Second, the TSN projects are still being developed although the evaluation has already started. This situation allows time for the before evaluation and leads to more contacts with TSN projects developers; it is an advantage for the precise understanding of the TSN projects components and action mechanisms. However, it is delaying the outcome and process evaluation criteria definition. Finally, the consortium has to be very careful, when dealing with interlocutors at the Ministry to keep full independence regarding strategic and methodological issues.

EvaTSN is a challenging French national research project for the production of evidenced-based information on HI technologies impact and on the context and conditions of their effectiveness and efficiency. We will be able to support health care management and policy decision making in order to implement HI technologies.

We will also be able to produce an evaluation toolkit for HI technology evaluation. This toolkit will consist in adequate study design and schedule for evaluation, appropriate evaluation criteria, data collection sources and means. It will be based on our EvaTSN large HI technology program evaluation experience.

